### Enrolment

Each subject is considered enrolled in the study the moment we obtain his/her consent to participate in the research by signing the informed consent to join the research. Recruitment will be carried out at IRCCS Medea, IRCCS Fondazione Stella Maris, Fondazione Don Carlo Gnocchi Onlus Rome, Fondazione Mondino, Centro S. Maria al Mare - Fondazione Don Carlo Gnocchi and Fondazione Don Carlo Gnocchi - IRCCS S. Maria Nascente.

### Statistical considerations

Data will be analysed using SPSS statistical software. Demographic data and the number of dropouts will be analysed using descriptive statistics. EMG and gait data will be analysed with standardised algorithms.

Data collected during the outcome assessments and the follow-up will be compared with T0 data (intra-group analysis). Furthermore, we will compare the results of the Control and Intervention groups (inter-group analysis). Appropriate statistical design will be used according to the normality of the dataset.

Since the Agilik orthosis is purposefully adjusted to increase knee extension as much as possible *above* what was achieved by a standard brace for each subject, we can be certain that the knee flexion will not worsen with it. We will consider an increase in KEMS greater than 8 degrees to be a clinically significant improvement. The trial is designed to find a significant difference for at least one of the two primary multiple endpoints. The standardized effect sizes for 6MWT and KEMS are assumed as 0.4 and 1.0 and the correlation of the two endpoints is assumed as 0.5 at a significance level of 0.025 with power = 0.80. Sample sizes obtained are  $n = 18$  for each group, with a total sample size required of  $2n = 36$ . Considering potential dropout (10%), we conservatively set the number of total participants at 40. The sample size estimation has been performed in R.

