## **Objectives and hypotheses of the clinical investigation**

The primary purpose of this study is to improve the clinical use of a powered extension assist knee ankle foot orthosis (Agilik) in individuals with knee extension deficiency due to cerebral palsy in a domiciliary setting. Considering the preliminary data available, we will specifically focus on improvement of anti-gravity knee extension in mid stance (KEMS) and endurance in patients with crouch gait due to CP. Therefore, the primary aim is to compare the KEMS and the endurance at baseline, after 2 months of Agilik training (intervention group) or standard care/daily life activities (control group) and after one month of follow-up.

The secondary aim is to compare the two groups in terms of joint ROM and muscle length, spasticity, postural and motor abilities, gait speed and pattern and self-perceived performance.

Finally, the third aim is to evaluate the usability and the acceptability of the exoskeleton within the intervention group. Also some evidence about the user experience with the technology will be collected, encompassing the subjective perspective of both the patient and the caregivers.

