### **Endpoints and measured variables**

In order to demonstrate the clinical improvement due to the use of the device, we will consider the following primary endpoints:

- Distance walked during a 6-minutes walking test (6MWT);
- The KEMS measured during gait analysis assessment

---

 Enright, Paul L. "The six-minute walk test." Respiratory care 48.8 (2003): 783-785

In addition, secondary endpoints will be considered with the following purposes:

- at T0 (baseline), T1 (post intervention) and at T2 (follow-up)
  - Measurements of the Joint ROM and muscle lengths
  - To determine the level of spasticity in the lower limbs with the Modified Ashworth scale (MAS)
  - To assess postural and motor abilities with Gross Motor Function Measure-88 (GMFM-88)
  - To assess functional gait assessment (walking speed) with the 10-meter walking test (10mWT)
  - To evaluate kinematics and kinetics assessments (gait pattern) with the 3D gait analysis overground with EMG data acquisition
  - To determinate self-perception of performance in everyday living with Canadian Occupational Performance Measure (COPM)
  - To quantify static balance with Centre of Pressure (COP) detection using the force platforms of the gait analysis lab when available
- at T1 only in the Intervention Group:
  - to assess the usability and acceptability of Agilik in parents/caregivers with the System Usability Scale (SUS) and the Technology Acceptance Method 3 (TAM-3)
  - to investigate aspects of behavioural engagement during the use of the Agilik device at home with semi-structured interviews with patients and their families

Only parents/caregivers of participants in the intervention group will be provided with a diary to freely explore, during the training, their thoughts and feelings about the device, in order to have a more extensive monitoring of the treatment.

Finally, an exploratory outcome will be:

- to perform a remote monitoring of gait behavior with sensorized shoes by Magnes (MAGNES AG, [name]). If possible, during the months between T0 and T1 we will ask the participants of both groups to wear the shoes during indoor and outdoor walking, allowing us to acquire gait data to assess spatiotemporal parameters during daily life.

---

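### The protocol states one level, 0.025, for two primary endpoints with no rule for passing alpha on; Holm's step-down test would give the 6MWT more power at no cost

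*Protocol*

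**What the plan says.** The Objectives section names both outcomes in the primary aim: "we will specifically focus on improvement of anti-gravity knee extension in mid stance (KEMS) and endurance in patients with crouch gait due to CP". The Endpoints and measured variables section lists both as primary: "Distance walked during a 6-minutes walking test (6MWT") and "The KEMS measured during gait analysis assessment". The design is described as confirmatory.

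The success rule is in Statistical considerations: "The trial is designed to find a significant difference for at least one of the two primary multiple endpoints". The planning inputs follow: "The standardized effect sizes for 6MWT and KEMS are assumed as 0.4" and 1.0 respectively, and "the correlation of the two endpoints is assumed as 0.5 at a significance level of 0.025 with power = 0.80". The result is 18 per group, 36 in total, raised to 40 for 10% dropout.

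That section does not say whether 0.025 is one- or two-sided, or whether it applies to each endpoint or to the pair. It names no multiplicity procedure. On the analysis itself, it says only that the method will depend on whether the data are normal.

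**The concern.** With two primary endpoints and success on either, some multiplicity control is needed. The only level that the protocol gives is 0.025. A reader who applies it as it stands would test each endpoint at 0.025 and stop there, which is an equal Bonferroni-type split.

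Such a split gives away most when the two effects are very unequal, as assumed here. KEMS (effect 1.0) will usually succeed, its share of alpha is then no longer needed, and the 6MWT (effect 0.4) is still judged at 0.025. Suppose KEMS is clearly significant and the 6MWT p-value is 0.04. The equal split gives no claim on endurance. Holm's test, with the same family-wise error, gives one. Endurance is half of the primary aim and the half with less power, so this is where unused alpha would help.

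**Working it through.** **Inputs (Statistical considerations).** n = 18 per group; effects 0.4 (6MWT) and 1.0 (KEMS); correlation 0.5; level 0.025; target power 0.80 for at least one endpoint.

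**Step 1: the protocol's own figure.** Under the normal approximation the test statistics have means 0.4 × √(18/2) = 1.2 and 1.0 × √(18/2) = 3.0. At-least-one power is 1 − P(both fail) under a bivariate normal with correlation 0.5.

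- Two-sided 0.025 per endpoint: 80% needs n = 18.76, so 19 per group; power at 18 is 78.2%.
- One-sided 0.025 per endpoint: 80% needs n = 15.35, so 16 per group; power at 18 is 85.7%.
- With t-tests, the two-sided reading needs 20 to 21 per group (about 75% at 18) and the one-sided reading needs 17 (83.8% at 18).

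The two-sided reading under the normal approximation comes closest to 18 and 80%, but no reading gives exactly 18, so the sample size does not settle what 0.025 means. The dropout step reproduces: 36 / (1 − 0.10) = 40.

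**Step 2: why Holm costs nothing.** Under the two-sided per-endpoint reading, Holm tests the smaller p-value at 0.025 and, if that is significant, the other at 0.05.

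- If both nulls are true, Holm rejects something only when the smaller p-value is at most 0.025, exactly as the equal split does. The simulated error is about 4.6% to 4.7% for both.
- If one null is true, it is tested at no more than 0.05.
- The first step is the same, so the power for at least one endpoint and the required n are the same.

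**Step 3: size of the gain.** 6MWT power under Holm = P(p₆ₘ ≤ 0.025) + P(0.025 < p₆ₘ ≤ 0.05 and p_KEMS ≤ 0.025). The results below use t-tests on 34 df, 18 per group, with Holm simulated over 400,000 replicates.

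| Reading of 0.025 | Holm levels | 6MWT, equal split | 6MWT, Holm | At least one (both methods) |
|---|---|---|---|---|
| Two-sided, per endpoint | 0.025, then 0.05 | 13.9% | 20.5% | 74.9% |
| One-sided, per endpoint | 0.025, then 0.05 | 21.4% | 31.1% | 83.8% |
| Two-sided, overall | 0.0125, then 0.025 | 8.7% | 13.1% | 64.9% |

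An overall one-sided 0.025 gives the same figures as the first row, because one-sided 0.0125 and 0.025 use the same critical values as two-sided 0.025 and 0.05.

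The gains are 20.5 − 13.9 = 6.6, 31.1 − 21.4 = 9.7 and 13.1 − 8.7 = 4.4 percentage points. In the first row, power to win on both endpoints rises from 13.0% to 20.1%, and KEMS power moves from 74.1% to 74.5%.

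**Step 4: checks.** In the first row, Holm cannot exceed the power of the 6MWT tested alone at two-sided 0.05, which is 21.4%, so 20.5% recovers nearly all that is available. Under the normal approximation the same row reads 14.9% to 21.6%. If all 40 complete (20 per group, t-tests), it reads 15.4% to 22.7%.

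**Step 5: what remains.** For 80% power on the 6MWT alone, n per group = 2(z₁₋α/₂ + z₀.₈)² / 0.4². At two-sided 0.025 this is 2 × (2.241 + 0.842)² / 0.16, about 119; at two-sided 0.05 it is 2 × (1.960 + 0.842)² / 0.16, about 99.

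**The case against.** A reader might infer that the protocol fixes a single-step test at 0.025 for each endpoint, so that the 6MWT can never receive freed alpha and a p-value between 0.025 and 0.05 must be called negative. The document does not support that. The 0.025 appears only as an input to the sample-size calculation. No single-step rule is named, and nothing bars passing alpha on. Because Holm's first step is the equal split, a sponsor who planned Holm would have written the same sample-size paragraph. The detail may also sit in a statistical analysis plan, which is not at hand.

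Three further objections have force. An equal split controls the family-wise error and fits the stated success rule, so using one would not be an error. The size of the gain depends on an unstated convention. Sidedness also has to match: if 0.025 was meant as one-sided per endpoint, a two-sided Holm test at 0.025 then 0.05 gives the 6MWT 20.5%, which is no better than the 21.4% it already has.

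All of this limits the point to an improvement. It does not remove it: the protocol states one level and no rule for the second endpoint, and Holm on the same footing is never worse than applying that level to each.

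**Conclusion.** This is a free improvement, not the correction of an error. The protocol gives one level for two primary endpoints and no provision for passing alpha on. Testing both at that level would be valid but would leave 6MWT power unused. Holm raises it from about 14% to about 20% (two-sided per endpoint), about 21% to 31% (one-sided per endpoint) or about 9% to 13% (overall two-sided).

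These figures assume 18 per group, the protocol's effects of 1.0 and 0.4, correlation 0.5 and t-tests. The direction of the gain does not depend on the reading of 0.025. The power for at least one endpoint, the sample size and the family-wise error bound are unchanged. Holm does not make endurance adequately powered: under every reading the 6MWT stays far below 80%.

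**What to change.** Add one sentence to Statistical considerations, and carry it into the statistical analysis plan: the two primary endpoints are tested by Holm's procedure, the smaller p-value at 0.025 and, if it is significant, the other at 0.05. If 0.025 was meant as the overall level, the steps are 0.0125 and then 0.025. State whether the tests are one- or two-sided, and use the same sidedness at both steps. If the statistical analysis plan already specifies a step-down test, it is enough to align the protocol with it.

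The cost is that sentence, with no added patients, visits or data. It should be fixed before any outcome data are seen by group, because a step-down rule adopted after a 6MWT p-value between 0.025 and 0.05 would not be credible.

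An unequal split favouring KEMS is not part of this recommendation. It would raise the power for at least one endpoint, but it would lower the chance of a 6MWT claim if KEMS has no effect, so it is a trade-off.

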### Information on subjects

We will enroll 40 children with knee extension deficiency due to CP according to sample size calculation.

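### The sample-size inputs do not reproduce 18 per group at 80% power: with two-sided 0.025 per endpoint, power is about 75% to 78%, and the meaning of the 0.025 level is not stated

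*Protocol*

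**What the plan says.** All the inputs are in the protocol's Statistical considerations section. The success rule is that "The trial is designed to find a significant difference for at least one of the two primary multiple endpoints". On the effects it says "The standardized effect sizes for 6MWT and KEMS are assumed as 0.4", followed by 1.0 for KEMS, and then "the correlation of the two endpoints is assumed as 0.5 at a significance level of 0.025 with power = 0.80". The result is 18 per group and 36 in total. The last step is "Considering potential dropout (10%), we conservatively set the number of total participants at 40".

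The section on subjects relies on the result: "We will enroll 40 children with knee extension deficiency due to CP according to sample size calculation".

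The test is left open: "Appropriate statistical design will be used according to the normality of the dataset". The general description of the design calls the trial confirmatory. The protocol does not say whether 0.025 is one- or two-sided, whether it applies to each endpoint or to the trial as a whole, or whether the calculation used a known-variance formula or t-tests.

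**The concern.** When a trial can succeed on either of two endpoints, two numbers depend on how the level is applied: the power at a given size, and the chance of at least one false positive. The stated inputs look complete, so a reader should be able to recover 18 from them. If they cannot, either the stated 80% power or the implied error control is not what the protocol says. In a confirmatory trial both should be readable from the design section. The 40 children are justified by this calculation alone.

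**Working it through.** **Inputs** (Statistical considerations): d1 = 0.4 for 6MWT, d2 = 1.0 for KEMS, correlation 0.5, level 0.025, target power 0.80, success on at least one endpoint, equal groups, n = 18 per group.

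**Formula.** With known variance, each test statistic has mean d × √(n/2). The two statistics are bivariate normal with correlation 0.5. For a one-sided critical value c on each endpoint:

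power = 1 − P(Z1 < c − d1√(n/2) and Z2 < c − d2√(n/2)).

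At n = 18, √(18/2) = 3, so the means are 0.4 × 3 = 1.2 and 1.0 × 3 = 3.0. Wrong-direction rejections are ignored. The t-test figures come from 400,000 simulated trials per setting.

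**Attempt to reproduce 18.**

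*Reading A: two-sided 0.025 per endpoint (0.05 shared equally).* This is one-sided 0.0125 on each, c = 2.241. The limits are 2.241 − 1.2 = 1.041 and 2.241 − 3.0 = −0.759. The joint probability of missing both is 0.218, so power is 1 − 0.218 = 0.782.

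*Reading B: one-sided 0.025 per endpoint.* c = 1.960. The limits are 0.760 and −1.040. The joint miss probability is 0.143, so power is 0.857.

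| n per group | A, normal | A, t-test | B, normal | B, t-test |
|---|---|---|---|---|
| 16 | 72.9% | 69.0% | 81.6% | 79.1% |
| 17 | 75.7% | 72.0% | 83.7% | 81.6% |
| 18 | 78.2% | 75.0% | 85.7% | 83.9% |
| 19 | 80.5% | 77.5% | 87.5% | 85.8% |
| 20 | 82.6% | 79.9% | 89.0% | 87.5% |
| 21 | 84.5% | 82.1% | 90.4% | 89.0% |

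The smallest n reaching 80% is 19 (A, normal), 20 to 21 (A, t-test; 79.9% at 20), 16 (B, normal) and 17 (B, t-test). None is 18.

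**Variants of A, normal formula, correlation 0.5.** A Sidak critical value gives 78.3% at 18 and needs 19. A correlation-adjusted critical value (c = 2.212) gives 79.1% at 18 and also needs 19. If 0.025 were a two-sided overall level and then shared (one-sided 0.00625 each), power at 18 would be 69.8% and 23 would be needed.

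**What does return 18.** Reading A with the normal formula and a correlation of 0 gives 80.9% at 18 and 78.5% at 17. A correlation of 0.1 gives 80.3% at 18 and also returns 18. At 0.3 power is already below target (79.1%). The stated correlation is 0.5.

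**Family-wise error at correlation 0.5** (both effects null): two-sided 0.025 on each endpoint, about 4.6%; one-sided 0.025 on each, about 4.5%; one-sided 0.0125 on each, about 2.3%.

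**Dropout.** 36 / 0.9 = 40, so that step is correct. With equal groups, 40 evaluable children means 20 per group.

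**The case against.** The strongest reply is that 18 is close to what the standard formulas give. Under Reading A with the normal formula the gap is one child per group. Small changes also return 18: a KEMS effect of 1.03, which would print as 1.0, gives 80.7% at 18, and a 60/40 division of the level in favour of KEMS gives 80.1%. The R code is not in the document. This stands as a reason not to guess how 18 arose, and in particular not to assert that the correlation was set to zero. But neither variant is stated, and the inputs as printed do not give 18.

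A second reply is that 0.025 may be a one-sided 0.05 shared between two endpoints. Then 18 exceeds 80% power with t-tests (83.9%) and error stays under 5%. That is a coherent design, and the protocol's remark that knee flexion cannot worsen with the device fits a directional test. It has to be stated, though, because it claims one-sided 5% and not one-sided 2.5%.

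Third, the 75% depends on t-tests, and the protocol leaves the test open. That is why the shortfall is given as a range. With variance estimated from about 36 children, the t-test figure is the more realistic end.

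A reader might go further and infer a false-positive rate of about 9%. That figure arises only if each endpoint is tested two-sided at 0.05. The protocol names 0.025, and at 0.025 per endpoint, one- or two-sided, the rate is about 4.5% to 4.6%. The documents do not support the 9%.

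**Conclusion.** The point holds in a limited form. Taken as printed, with equal levels on the two endpoints, the inputs lead to 16, 17, 19 or 20 to 21 per group, depending on the reading, and not to 18. Under the usual reading (two-sided 0.05 shared equally), power with 18 evaluable per group is about 78% by the normal formula and about 75% with t-tests, a shortfall of 2 to 5 points. It reaches about 80% with t-tests only if there is no dropout, while the protocol itself allows for 10%. Under one-sided 0.025 per endpoint the power is adequate, but family-wise error is controlled at one-sided 0.05 and not at 0.025.

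These figures assume that the stated effects and correlation are true, equal groups and normally distributed outcomes. The issue is a misstated power and an undefined level. It does not show uncontrolled error or call for more children, so it is worth correcting but is not critical.

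**What to change.** In Statistical considerations, state the level as two-sided 0.025 for each of the two primary endpoints, with a family-wise level of 0.05. Replace the stated power of 0.80 with: about 75% with 18 evaluable per group, and about 80% if all 40 are evaluable (t-tests, correlation 0.5). Keep 40 participants.

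The sponsor should first check the R calculation. If it used a one-sided level, the protocol should say so, name the family-wise level that it controls, and give the matching power (about 84% with t-tests at 18 per group for one-sided 0.025 on each endpoint). If it used unequal levels or less rounded effects, those should be printed.

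The cost is a sentence or two of wording and, under the two-sided reading, a slightly less favourable power figure. No extra children and no design change are needed.

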### Data management

The indispensable data to finalise the investigation, in particular personal and health data, will be processed in compliance with EU Regulation 2016/679, (GDPR) and Legislative Decree 10 August 2018, no. 101.

During data collection, the PI of each clinical site will pseudonymise the data, identifying the subjects recruited with codes, or adopting other solutions that comply with point 5.4 of the Privacy Guarantor's Order No. 146/2019. Indeed, the use of encryption techniques allows to store and process the subject's information, preventing the identification by any person outside the Institute. Only the PI and authorised personnel can link each code to the name of the participant.

Project partners acting as autonomous data controllers may share information to each other in pseudonymised form and without identification data. Such transmission is configured as data communication and processing by third parties, which must be indicated by name and separately in the information on the processing of personal data.

Subjects who wish could know what information will be stored and in what manner. Access to the data will be allowed only to authorised personnel of the centre involved. At the end of the research, the study results concerning a participant to the investigation may be communicated to him or her, if requested.

All data collected during the course of this project will be kept for a minimum of 25 years past the closing of the protocol.

The above data will be entered in digitalized format, creating a specific eCRF in a Data Management System validated according to national legislation, already in use at IRCCS Medea. The platform used will be RedCap (Research Electronic Data Capture). The REDCap Consortium is made up of more than 1000 institutional partners around the world (research institutions, universities, ministries, etc.). The consortium supports a secure web application (REDCap) designed exclusively to support data capture for research studies. The REDCap application allows users to create and manage online databases quickly and securely, and it is currently in use for more than 110,000 projects with approximately 150,000 users covering numerous areas of research interest across the consortium. Through REDCap, for this study the following measures will be implemented:

- user-level identification, with specific restrictions based on role in the study;
- validation and control of data integrity in real time;
- de-identification of patients before data export;
- centralized data storage with daily backup. The compiler, in turn, will take responsibility for the non-disclosure and dissemination of the data.

### **Intellectual property**

The results of the study will be owned by all the clinical experimental centres that participate in the study.

